## Abstract

**Background:**

Irritable bowel syndrome (IBS) is one kind of common functional bowel disease with obscure pathogenesis, and exploration about whole transcriptome profiling in IBS-D is still negligible. Conventional medications have limited effects, which makes focus shifted to traditional Chinese medicine (TCM). Tong-Xie-Yao-Fang, as a classic herbal formula in TCM, is pretty effective and safe for the treatment of diarrhea-predominant irritable bowel syndrome (IBS-D), but the underlying therapeutic mechanism remains unknown. We aim to verify the efficacy and safety of TXYF granule (the formula particles mixed together) in IBS-D and elucidate the gene-level mechanism of IBS-D and therapeutic targets of TXYF granule based on whole transcriptome analysis.

**Methods/design:**

This is a randomized, double-blind, and placebo-controlled clinical trial consisting of 2 weeks of run-in period, 12 weeks of treatment period, and 8 weeks of follow-up period. We will enroll 120 participants with IBS-D, who will be randomly assigned to the TXYF granule group and the placebo group, and recruit additional 10 healthy individuals as controls for mechanistic outcome. The two groups respectively take TXYF granule or placebo orally for treatment. The primary outcome is the response rate of IBS-Symptom Severity Score (IBS-SSS). The secondary outcomes include adequate relief (AR), IBS-Quality of Life Questionnaire (IBS-QOL), and long-term efficacy. Mechanistic outcome is the whole transcriptome profiling of the intestinal mucosae from IBS participants before and after the treatment and healthy individuals.

**Discussion:**

This trial will prove the effectiveness and safety of TXYF granule with high-quality evidence and provide a penetrating and comprehensive perspective on the molecular mechanism of IBS-D by whole transcriptome analysis, which makes us pinpoint specific biomarkers of IBS-D and therapeutic targets of TXYF.

**Trial registration:**

Chinese Clinical Trial Registry ChiCTR-IOR-1900021785. Registered on 9 March 2019

## Background

As a common functional bowel disease, irritable bowel syndrome (IBS) is mainly characterized by intermittent abdominal pain, disturbed intestinal motility, and altered bowel habits, which can be elaborately categorized into four subtypes [1]. Thereinto, diarrhea-predominant irritable bowel syndrome (IBS-D) defined as loose or watery stools (precisely type 6 or type 7 of Bristol stool form scale) appearing more than 1/4 of bowel movements (BM) and less than 1/4 of BM with type 1 or type 2 of Bristol stool form scale definitely is the most common subtype of IBS [2]. From the perspective of epidemiology, this nuisance ailment affects 10 to 15% of the population and females are predisposed to this disease [3]. IBS is a multifactorial disease, and many studies have demonstrated that visceral hypersensitivity [4], gut barrier dysfunction [5], aberrant microbiota-brain-gut interaction [6, 7], and intestinal motility abnormality [8] are the pivotal participators in the pathogenesis. Deserve to be mentioned, further studies at the gene level are imperative because they are conducive to decipher the aforementioned pathogenesis. Conventional medications for IBS-D, such as antidiarrheal, antispasmodic, antibiotics, and probiotics, often have limited effects and repeated treatment brings about tremendous socioeconomic pressure so that the therapeutic focus has naturally shifted to traditional Chinese medicine (TCM).

Tong-Xie-Yao-Fang (TXYF), a classic prescription in Chinese herbal medicine, consisting of four core herbs (*Rhizoma Atractylodis Macrocephalae*, *Paeoniae Radix Alba*, *Citri Reticulatae Pericarpium*, and *Saposhnikoviae Radix*), has been specially applied for mitigating abdominal pain accompanied with diarrhea in clinics for hundreds of years. TXYF accords with one kind of major pathogenesis known as liver depression and spleen deficiency of IBS-D in TCM theory. *Rhizoma Atractylodis Macrocephalae* and *Citri Reticulatae Pericarpium* strengthen the spleen to eliminate dampness while *Paeoniae Radix Alba* and *Saposhnikoviae Radix* soothe the liver to regulate qi. These four herbs contained in TXYF by orchestrating the function of the spleen and liver to relieve symptoms of IBS-D. A recent study has proved that TXYF is efficacious in the relief of abdominal pain and bloating in IBS-D patients with only sporadic adverse events [9]. But there is a scrap of contradictory evidence that TXYF has little impact on the amelioration of symptoms of IBS-D [10]. Meanwhile, it has been demonstrated in IBS-D rat models that TXYF can regulate the level of 5-HT and SP with respect to visceral hypersensitivity and TXYF can modulate the intestinal flora by downregulating the ratio of *Firmicutes* to *Bacteroidetes* and the fecal abundance of *Clostridium* [11, 12]. Moreover, TXYF has been proved to ameliorate intestinal permeability by inhibiting inflammation-related NF-κB and notch pathways [13]. However, heterogeneity about the constitution and the dose of TXYF exists in previous studies. TXYF therapeutic targets and molecular mechanisms directing IBS-D have not been profoundly illuminated.

About 75% of human genes can be transcribed, and transcriptome landscape is the direct reflection of encoded genetic information [14]. Transcriptome profiling is able to comprehensively unveil the pathogenesis of IBS-D and the targets of traditional Chinese medicine by analyzing the interaction networks of differentially expressed protein-coding RNAs and noncoding RNAs (ncRNAs). Two pilot studies show that by using RNA-seq and RT-PCR, there is a discrepancy in rectosigmoid/small bowel mucosal mRNA expression between IBS-D patients and controls, mainly involving neurotransmitters, intestinal immunity, barrier function, ion transport, and so on [15, 16]. In the WAS-induced IBS rat model, the transcriptome profile demonstrates that the majority of differentially expressed genes relate to notch signaling and focal adhesion by employing mRNA microarray analysis [17].

Along with the blooming of the RNA sequencing technology, noncoding RNAs, previously thought to be “transcriptional noise,” actually have been proven crucial to transcriptional and post-transcriptional events of gene expression and genome maintenance [18]. More and more studies have given insights into the indispensable roles of ncRNAs played in the cellular process [19], tumorigenesis [20], inflammatory regulation [21], and so on. Our previous studies also have reported that microRNA-144 and microRNA-200a are involved in intestinal permeability and visceral hyperalgesia separately by binding to specific target mRNA in IBS-D rats [22, 23]. However, exploration about ncRNAs for IBS-D is still negligible. Few studies shed light on the function of long noncoding RNA and circular RNA in the pathogenesis of IBS-D. Nor do researchers probe the whole transcriptome profiling for targets or pathways of TCM in IBS-D. In the current trial, we attempt to verify the efficacy and safety of TXYF granule (the formula particles mixed together) for the treatment of IBS-D, which syndrome differentiated as liver depression and spleen deficiency, and elucidate the underlying mechanism of IBS-D and seek out therapeutic targets of TXYF granule based on whole transcriptome analysis.

## Methods/design

### Study design and recruitment

This clinical study is a single-center, randomized, double-blind, and placebo-controlled trial comparing TXYF granule with placebo in patients with IBS-D, which will be performed lasting totally 22 weeks. At the initial run-in period (weeks − 2–0), we will assess eligibility and seek informed consent. Then, coming to the treatment period (weeks 0–12), eligible subjects will be randomly assigned to one of two groups (TXYF granule group and placebo group) in a 1:1 ratio and get blinded treatment of 12 weeks. Finally, we will have a follow-up (week 20) 2 months after the treatment. This study involves 6 site visits (week − 2, week 0, week 4, week 8, week 12, and week 20) and 12 call visits (weekly call follow-up during the treatment period); eventually, the primary outcome and the secondary outcome will be evaluated. We will obtain the intestinal mucosae from partial IBS-D patients (*n* = 10 for each group) before and after treatment for the assessment of mechanistic outcome. The process of the study and visit schedule are schematically shown in Figs. 1 and 2. This clinical trial protocol refers to The Standard Protocol Items: Recommendations for Interventional Trials (SPIRIT) 2013 Checklist detailed in Additional file 1.

**Fig. 1 Fig1:**
[figure not shown]
Flowchart of the trial: 120 eligible subjects will be randomly allocated into the TXYF granule group and placebo group in a 1:1 ratio, from which 10 participants of each group randomly will be selected to undergo mechanistic assessment. Colonic samples will be obtained from each group of 10 participants (pre- and post-treatment) and 10 healthy controls for RNA-seq and whole transcriptome analysis

**Fig. 2 Fig2:**
[figure not shown]
Recommended protocol items: visit schedule for enrollment, interventions, and assessments

All 120 IBS-D patients participating in this study will be recruited from the gastroenterology department or ward at the First Affiliated Hospital of Guangzhou University of Chinese Medicine. And we will additionally recruit 10 healthy controls who will undergo intestinal mucosal biopsy for investigation of transcriptome profiling. Written informed consent which contains additional provisions for collection and use of colon samples will be obtained from each participant before enrollment. The trial process conforms to the Declaration of Helsinki (2008) [24]. The Clinical Trials and Biomedical Ethics Committee of the First Affiliated Hospital of Guangzhou University of Chinese Medicine (No.ZYYECK YJ [2018]125) has approved our trial.

### Eligibility criteria

#### Inclusion criteria

Patients have to satisfy the diagnostic criteria of IBS-D defined by ROME IV [25].The score of IBS-Symptom Severity Score (IBS-SSS) is more than 75 at baseline visit [26].Patients have to satisfy the diagnostic criteria of diarrhea syndrome with liver depression and spleen deficiency based on TCM syndrome differentiation [27].The age is between 18 and 70 years old.Patients must make an agreement to participate and sign a written informed consent.

#### Exclusion criteria

Patients have a history or current evidence of inflammatory bowel disease, gastrointestinal bleeding, or abdominal surgery.Patients have a history or current evidence of other organ diseases which influence gastrointestinal motility, such as hyperthyroidism, diabetes, and chronic renal impairment.Patients have a history or current evidence of serious damages of the heart, liver, kidney, blood system, or immune system.Patients used therapeutic medications for IBS-D or other diseases which could affect the trial within 2 weeks before enrollment.Patients are currently pregnant and lactating.Patients have an allergy to trial medication.Patients have a history of neurological disease or mental illness.Patients have participated in other clinical studies.

### TCM syndrome differentiation

TXYF is typically applied to IBS-D patients with liver depression and spleen deficiency according to the expert consensus on diagnosis and treatment of irritable bowel syndrome in traditional Chinese medicine (2017) [27]. Patients who have two primary symptoms plus one secondary symptom, integrated with signs of the tongue and pulse, will be differentiated as syndrome of liver depression and spleen deficiency and enrolled:
Primary symptoms: (1) abdominal pain accompanied by diarrhea and (2) prone to irascible or irritableSecondary symptoms: (1) distending pain in hypochondrium, (2) reduced appetite, and (3) presented with fatigueAuxiliary symptoms: light and enlarged tongue or tooth-marked tongue with white greasy coating, string pulse

### Randomization and blinding

Randomization scheme that generates a list of 120-case randomization sequence utilizing the stratified block randomization method by computer will be implemented by an independent statistician, which guarantees that enrolled patients will be evenly allocated to the TXYF granule group or the placebo group. Then, 10 participants of each group will be randomly selected for RNA sequencing and whole transcriptome analysis. Concealment of allocation code relies on an opaque envelope. This trial requires that all participants and researchers involved in drug distribution, outcome evaluation, and data analysis are completely blinded to allocation. The occurrence of severe adverse events or other unpredictable events allows unblinding under the permission of the principal investigator.

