### Intervention

TXYF granule or placebo will be orally administered one packet (strength, 8.1 g) after dissolved twice a day (1 h after the meal) for 12 weeks. Over the course of the study, participants are required to discontinue therapeutic medications associated with IBS-D. Simultaneously, probiotic foods, functional foods, and dietary supplements are also prohibited. Participants are obligated to fill in the study diary daily involving medication administration record, concomitant treatments, and dietary questionnaire which avail to check compliance and statistically rectify dietary bias. Onset of exacerbated IBS-D symptoms allows rescue medications for less than 1 week, which needs to be documented in the electronic Case Report Form (eCRF).

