### Outcome measurements

#### Primary outcome

The primary outcome of our trial is the response rate of IBS-Symptom Severity Score (IBS-SSS). A responder is defined as a 50% or more reduction in IBS symptoms compared to baseline [28]. IBS-SSS is a hitherto unique symptom severity questionnaire of IBS, which evaluates the condition of abdominal pain, abdominal distension, and defecation satisfaction. This definition of a responder that reports a 50% or more reduction in IBS symptoms is less disturbed by the initial severity of IBS. IBS-SSS will be assessed at baseline, week 4, week 8, week 12, and week 20 while the response rate of IBS-SSS will be assessed at week 4, week 8, week 12, and week 20.

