### Statistical analysis

#### Clinical data analysis

Based on the principle of intention-to-treat (ITT), all randomly assigned participants will be included in the statistical analysis. For participants who prematurely terminate this trial, outcomes of the last visit will be used as the final outcomes. Statistical analyses will be completed by SAS (version 9.4, SAS Institute, Cary, NC). Continuous variables will be presented in the form of means and standard deviations while the categorical variables will be presented in the form of counts and percentages. The primary outcome (week 4, week 8, week 12, and week 20) and the secondary outcome AR (week 12) will be assessed by using *χ*^2^ test or Fisher’s exact test. Another secondary outcome IBS-QOL (baseline, week 4, week 8, week 12, and week 20) will be assessed by using *T* test or Mann-Whitney *U* test accompanied with the Wilcoxon test. A two-sided *P* < 0.05 indicates statistical significance. For missing data, sensitivity analysis will be conducted and the optimal approach to the imputation of missing data will be proposed.

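### The primary and AR tests ignore the strata used in randomisation, and none of the named clinical tests can carry the promised dietary correction

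*Protocol article*

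**What the plan says.** All places are in the protocol article.

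- **Randomization and blinding:** an independent statistician runs a scheme that "generates a list of 120-case randomization sequence utilizing the stratified block randomization method by computer". Study design and recruitment gives the allocation: "eligible subjects will be randomly assigned to one of two groups (TXYF granule group and placebo group) in a 1:1 ratio". The same section says "This clinical study is a single-center, randomized, double-blind, and placebo-controlled trial", so centre cannot be the stratification factor. The article names no factor.
- **Primary outcome:** the endpoint is binary. "A responder is defined as a 50% or more reduction in IBS symptoms compared to baseline".
- **Clinical data analysis:** the primary outcome and AR "will be assessed by using *χ*^2^ test or Fisher’s exact test". IBS-QOL gets a t test or Mann-Whitney test, together with a Wilcoxon test. No stratified test, model or covariate is named for any clinical outcome. All randomised patients are analysed, with the last visit carried forward.
- **Intervention:** "Participants are obligated to fill in the study diary daily involving medication administration record, concomitant treatments", and a "dietary questionnaire which avail to check compliance and statistically rectify dietary bias".

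**The concern.** Stratified allocation makes the arms more alike on the strata than chance would. If those strata predict response, the difference between arms varies less than a simple two-sample test assumes. The test then uses too large a standard error, rejects a true null hypothesis less often than 5%, and gives up power that the design has already paid for. The article fixes this test by name, so it is a stated choice and not a detail left open.

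The dietary correction is a second mismatch. One section says diary data will be used to correct for diet; the analysis section lists only tests that cannot do so. If the diet data used were those recorded on treatment, they would come after randomisation. The Discussion calls diet a trigger of IBS-D, and reduced appetite is among the secondary symptoms of the TCM syndrome being treated. Treatment could therefore plausibly change diet, and adjusting for a variable that treatment has changed can distort the comparison between arms.

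**Working it through.** **1. The plan's own figure.** Inputs from Sample size calculation: 70% v 40%, 80% power, 5% type I error, taken as two-sided as in Clinical data analysis. With a pooled rate of 0.55:

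n = [1.960·√(2·0.55·0.45) + 0.842·√(0.70·0.30 + 0.40·0.60)]² / 0.30² = 41.97, so 42 per group.

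For 15% drop-out, 42/0.85 = 49.4, so 50 per group and 100 in total. Both figures match the article. They are the size for an unstratified test.

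**2. Assumed strata.** The article gives neither factors nor effects. I assume two equal strata, 30 per arm in each (60 per arm, N = 120, because all randomised patients are analysed). Placebo response averages 40%, split 40/40, 30/50, 20/60 or 15/65.

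**3. Why the plain test is conservative.** The plain test uses the pooled variance p(1−p) = 0.40·0.60 = 0.24. The variance that remains within balanced strata is the average of p(1−p) over the strata. The effective critical value is 1.960/√(within/pooled).

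| Placebo rates | Within-stratum variance | Ratio to 0.24 | Effective critical value | Approximate type I error |
|---|---|---|---|---|
| 30/50 | (0.21 + 0.25)/2 = 0.230 | 0.958 | 2.00 | 4.5% |
| 20/60 | (0.16 + 0.24)/2 = 0.200 | 0.833 | 2.15 | 3.2% |
| 15/65 | (0.1275 + 0.2275)/2 = 0.1775 | 0.740 | 2.28 | 2.3% |

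**4. Simulation, chi-square v CMH (no continuity correction).** For power, a common odds ratio across the strata is set so that the treated rate averages the planned 70%. The treated rates by stratum are then 61/79, 53/87 and 49/91.

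| Placebo rates | Type I, chi-square v CMH | Power, chi-square v CMH | Power lost |
|---|---|---|---|
| 40/40 (not prognostic) | 5.0% v 5.0% | 92.4% v 92.4% | 0 |
| 30/50 | 4.6% v about 5% | 92.9% v 93.0% | 0.1 points |
| 20/60 | 3.2% v 5.0% | 94.0% v 95.5% | 1.5 points |
| 15/65 | 2.3% v 5.0% | 95.1% v 97.3% | about 2.3 points |

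Enumerating all possible outcomes, instead of simulating, gives the same results to within about 0.1 point. A still stronger split, 10/70, gives type I error of 1.4% v 5.0% and power of 96.1% v 98.7%, a loss of 2.6 points.

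**5. Smaller sample.** With 42 per arm and placebo rates of 18/62, power is 85.2% v 87.8%, again a loss of 2.6 points.

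**6. Diet.** No arithmetic applies, since no diet variable, model or effect is given. Of the tests named for clinical outcomes (chi-square, Fisher, t, Mann-Whitney, Wilcoxon), none takes a covariate, so the correction mentioned under Intervention has no counterpart in the analysis section.

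**The case against.** The strongest reply is that this matters little here.

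- The error is on the safe side.
- The unstratified test agrees with the basis of the sample size.
- Strong strata are not documented. The trial has one centre, one IBS subtype and one TCM syndrome, and the article itself says the 50% responder definition is less sensitive to initial severity, which weakens the most obvious candidate factor. With 30/50 strata almost nothing is lost.

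All of that stands, and it limits the size of the point. It does not remove the mismatch between a stated design and a stated test.

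Three stronger readings are tempting, but the documents do not support them.

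- **A large loss of power.** A reader could reach one by assuming a treatment effect well below the plan. The only effect in the article is 40% v 70%, and there the loss is small.
- **A 120-case list is not a stratified scheme.** A list of 120 can be made up of separate block sequences, one per stratum, and nothing says otherwise. Unnamed factors and block sizes are details that an article may leave to the full protocol.
- **The trial will adjust its primary result for on-treatment diet.** The article does not say which diary days or which analysis would be used. The diary may also cover the two-week run-in, and an unseen SAP could contain a supplementary model.

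**Conclusion.** The point holds as an efficiency mismatch. Allocation is stratified, and the test fixed for the primary outcome and AR ignores the strata. If the strata are prognostic, type I error falls to about 4.6% to 2.3% over the 30/50 to 15/65 range. At the planned effect with 60 per arm, the power cost is 0.1 to about 2.3 points, and power stays above 92% throughout. False positives are not inflated, so a significant result would not be put in doubt. These figures rest on two equal, fully balanced strata with assumed response rates; if the strata do not predict response, nothing is lost.

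The dietary part holds as an inconsistency between two sections. The risk of bias is conditional: it arises only if diet recorded during treatment enters an adjusted comparison, and its direction cannot be derived from the article.

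**What to change.** In Clinical data analysis, make the test for the IBS-SSS response rate and for AR a CMH test stratified by the randomisation factors, or a logistic regression that includes them. Report a stratified risk difference with its 95% CI.

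Reconcile the Intervention section with the analysis section. Either drop the dietary correction, or name the model and restrict it to diet recorded before randomisation, in the run-in. Report on-treatment diet by arm descriptively.

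The cost is a few lines of text and trivial programming, settled before unblinding. The treatment comparison needs no new data, and the sample size need not change. If the strata turn out not to be prognostic, the stratified test gives up nothing material at N = 120 (power 92.4% either way). A pre-randomisation dietary adjustment does require that the diary or questionnaire be completed during the run-in, which should be confirmed.

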### Experimental medication preparation and quality control

TXYF granule and placebo are uniformly manufactured by Guangdong YiFang pharmaceutical co., LTD under the guidance of Good Manufacturing Practices (GMP), which have the identical appearance and nearly similar taste. TXYF granule is made up of *Rhizoma Atractylodis Macrocephalae*, *Paeoniae Radix Alba*, *Citri Reticulatae Pericarpium*, and *Saposhnikoviae Radix* (see Table 1). These four crude herbs are weighed in proportion of the prescription, subsequently washed, and crushed, and the thickness of the slices is 0.3–1.5 cm. *Rhizoma Atractylodis Macrocephalae* and *Paeoniae Radix Alba* are fired while *Citri Reticulatae Pericarpium* and *Saposhnikoviae Radix* are raw for use. According to the optimized implementation scheme for decocting, extracting, and concentrating of the crude herbs, the ointments are prepared with a relative density of 1.07 to 1.09 g/ml, and then the ointments are screened to get granulated ointments. Finally, after spray drying and crushing, the granules are packed in sealed opaque packages. Placebo consisting of maltodextrin, dextrin, experimental medication extract (< 5%), kudingcha extract, and pigment is also prepared granules. The specific content is shown in Table 2.

**Table 1 Tab1:** Components of TXYF granule

Chinese name	Botanical name	Latin name	Part used	Source	Dosage (g)
Baizhu	*Atratylodes macrocephala macrocephala* Koidz.	*Rhizoma Atractylodis Macrocephalae*	Rhizome	Zhejiang	18
Baishao	*Paeonia lactiflora* Pall.	*Paeoniae Radix Alba*	Root	Sichuan	12
Chenpi	*Citrus reticulata* Blanco	*Citri Reticulatae Pericarpium*	Matured pericarp	Guangdong	9
Fangfeng	*Saposhnikovia divaricata* (Turez.) Schischk.	*Saposhnikoviae Radix*	Root	Neimeng	6

**Table 2 Tab2:** Components of the placebo

Ingredients	Component (%)
Maltodextrin	23.97
Dextrin	18.6
Starch	50.0
Experimental medication extract	5.0
Kudingcha extract	2.0
Pigment	0.43

The quality inspection department of Guangdong YiFang pharmaceutical company was responsible for the quality control of experimental medication based on pharmacopeia and national drug quality standards. Thin-layer chromatography and high-performance liquid chromatography-mass spectrometry were respectively utilized for qualitative and quantitative testing. Among them, the content of paeoniflorin in extract of *Paeoniae Radix Alba*, the content of hesperidin in *Citri Reticulatae Pericarpium* extract, and the total content of Prim-O-Glucnylcimifugin and 4′-O-β-glucosyl-5-O-Methylvismmiside in *Saposhnikoviae Radix* extract were 8.97%, 0.84%, and 0.7%, respectively. The microbial limit of each herb extract was qualified.

